## Abstract

**Background:**

Treatment for locally advanced rectal cancer (LARC) consists of chemoradiation therapy (CRT) and surgery. Approximately 15% of patients show a pathological complete response (pCR). Increased pCR-rates can be achieved through dose escalation, thereby increasing the number patients eligible for organ-preservation to improve quality of life (QoL). A randomized comparison of 65 versus 50Gy with external-beam radiation alone has not yet been performed. This trial investigates pCR rate, clinical response, toxicity, QoL and (disease-free) survival in LARC patients treated with 65Gy (boost + chemoradiation) compared with 50Gy standard chemoradiation (sCRT).

**Methods/design:**

This study follows the ‘cohort multiple randomized controlled trial’ (cmRCT) design: rectal cancer patients are included in a prospective cohort that registers clinical baseline, follow-up, survival and QoL data. At enrollment, patients are asked consent to offer them experimental interventions in the future. Eligible patients—histologically confirmed LARC (T3NxM0 <1 mm from mesorectal fascia, T4NxM0 or TxN2M0) located ≤10 cm from the anorectal transition who provided consent for experimental intervention offers—form a subcohort (*n* = 120). From this subcohort, a random sample is offered the boost prior to sCRT (*n* = 60), which they may accept or refuse. Informed consent is signed only after acceptance of the boost. Non-selected patients in the subcohort (*n* = 60) undergo sCRT alone and are not notified that they participate in the control arm until the trial is completed.

sCRT consists of 50Gy (25 × 2Gy) with concomitant capecitabine. The boost (without chemotherapy) is given prior to sCRT and consists of 15 Gy (5 × 3Gy) delivered to the gross tumor volume (GTV). The primary endpoint is pCR (TRG 1). Secondary endpoints include acute grade 3–4 toxicity, good pathologic response (TRG 1-2), clinical response, surgical complications, QoL and (disease-free) survival. Data is analyzed by intention to treat.

**Discussion:**

The boost is delivered prior to sCRT so that GTV adjustment for tumor shrinkage during sCRT is not necessary. Small margins also aim to limit irradiation of healthy tissue. The cmRCT design provides opportunity to overcome common shortcomings of classic RCTs, such as slow recruitment, disappointment-bias in control arm patients and poor generalizability.

**Trial registration:**

The Netherlands Trials Register NL46051.041.13. Registered 22 August 2013. ClinicalTrials.gov NCT01951521. Registered 18 September 2013.

## Background

Colorectal cancer is the second most common cancer in women and third in men worldwide [1]. Almost one-third of Dutch colorectal cancers are located in the rectum [2]. Rectal cancers are treated by surgery, preceded by chemoradiation in case of locally advanced rectal cancer (LARC). Chemoradiation consists of a total dose of about 50 Gy combined with capecitabine. With this treatment regimen, approximately 15% of patients show a pathological complete response (pCR) [3,4], classified by Mandard *et al*. as tumor regression grade 1 (TRG 1) [5]. In a recent meta-analysis, we showed that doses of ≥60 Gy were associated with an increased pCR rate to 20.4%, without compromising toxicity [6].

Patients with ‘good’ clinical response, either pCR (TRG 1) or near-pCR (TRG 2), might be eligible for organ-preserving approaches. The aim of these strategies is to deliver an optimal quality of life (QoL) without compromising the oncologic outcome in this favorable subgroup. Recently, several protocols have been developed, that use either local excision [7-9] or a “watch-and-wait” policy [10-12], in order to omit surgery (total mesorectal excision) as the primary treatment. In addition, patients who reach a pCR often show reduced local recurrence and improved (disease-free) survival probabilities compared with patients with a poor response (TRG 3–5) [3,13-15], possibly driven by a favorable tumor biology.

Thus, by escalating the preoperative radiation dose, the amount of patients with a ‘good’ clinical response or pCR who are eligible for organ-preserving treatment can potentially be increased. However, response rates after high-dose external radiation with 65 Gy have not yet been investigated in a randomized setting. Therefore, we set up an exploratory trial, the RandomizEd Controlled Trial for Pre-operAtive Dose-escaLation BOOST in Locally Advanced Rectal Cancer (RECTAL BOOST study: ClinicalTrials.gov NCT01951521) to compare tumor pCR rates (TRG 1), pathologic ‘good’ responses, toxicity levels, clinical tumor response and QoL between patients treated with 65 Gy chemoradiation (15 Gy boost plus 50 Gy chemoradiation) and those treated with 50 Gy standard chemoradiation therapy (sCRT).

## Methods/design

### Study design

This study is being conducted within the ProspectIve data CollectioN Initiative on Colorectal cancer (PICNIC) project [16]. The prospective observational PICNIC cohort includes patients with colorectal cancer of all stages. Information collected includes baseline demographic and clinical data, as well as prospective clinical follow-up and patient-reported outcome measures (PROMs). The study follows the cohort multiple randomized controlled trial (cmRCT) design [17] and provides a pragmatic infrastructure for multiple randomized controlled trials (RCTs).

### Patient recruitment

At enrollment in the PICNIC cohort, patients are asked to provide informed consent for prospective collection of clinical, survival and PROMs data. In addition, according to the cmRCT design, we ask patients’ consent to be randomly selected to receive offers on experimental interventions in the future and to use their data comparatively within the context of the PICNIC project.

From among the PICNIC cohort, we will identify all patients eligible for the boost intervention based on the following inclusion criteria: (1) histologically confirmed LARC, defined as T3 with threatened mesorectal fascia (<1 mm), T4 or N2M0 [18] (based on Dutch guidelines for chemoradiation in rectal cancer [19], in which N2 is defined as ≥4 positive nodes visible with diameter >9 mm or 5 to 9 mm combined with 2 of the following 3 characteristics: irregular border, heterogeneous or round-shaped); (2) tumor located ≤10 cm from the anorectal transition; and (3) previously obtained informed consent to be randomly offered experimental interventions within the context of the PICNIC project (Table 1). Patients are ineligible in case of inflammatory bowel disease, pregnancy, previous radiation to the pelvis, contraindication for capecitabine and inadequate comprehension of the Dutch language in speech and/or writing. Female patients in whom the tumor is located on the anterior wall close to the vagina are also ineligible because the maximum tolerated dose to the vagina does not allow for dose escalation when the tumor is in proximity to it.

**Table 1 Tab1:** **Inclusion and exclusion criteria for the RECTAL BOOST study**
^**a**^

**Inclusion criteria**	**Exclusion criteria**
Participant in the PICNIC project	Metastatic disease
Informed consent obtained for being offered experimental interventions within the PICNIC project	Inflammatory bowel disease
Informed consent obtained for questionnaires on patient-reported outcomes within the PICNIC project	Prior radiation to the pelvis
Tumor distance of ≤10 cm from anorectal transition	Inadequate understanding of the Dutch language in speech and/or writing
Indication for chemoradiation based on Dutch guidelines	Recent pregnancy ≤1 yr ago
No contraindication for MRI	No indication for chemoradiation based Dutch guidelines
World Health Organization performance status 0–2	At least one contraindication for capecitabine administration

^a^RECTAL BOOST, RandomizEd Controlled Trial for Pre-operAtive Dose-escaLation BOOST in Locally Advanced Rectal Cancer; PICNIC, ProspectIve data CollectioN Initiative on Colorectal cancer; MRI, Magnetic resonance imaging.

### Random selection

Patients within the PICNIC cohort who meet the above inclusion criteria form a subcohort of eligible patients (Figure 1). From among this subcohort, a random sample is selected on a 1:1 basis with varying block sizes (*n* = 6 to 8) using a centrally available computer program. Randomly selected patients are offered the experimental intervention (boost prior to sCRT) by their treating physician. If they accept the offer, they will sign an additional informed consent to receive the boost. Patients who refuse the boost will receive care as usual (that is, sCRT). Patients in the subcohort who will not be randomly selected will not be informed about the boost intervention, nor will they be informed about their participation in the control arm of this study. When the trial is completed, aggregate disclosure about the trial results will be provided to the entire PICNIC cohort at the same time.

**Figure 1 Fig1:**
[figure not shown]
**Study design and flowchart.** PICNIC, ProspectIve data CollectioN Initiative on Colorectal cancer; RECTAL BOOST, RandomizEd Controlled Trial for Pre-operAtive Dose-escaLation BOOST in Locally Advanced Rectal Cancer.

### Standard treatment

sCRT consists of 50 Gy (25 × 2 Gy on weekdays) combined with capecitabine. The radiation dose is delivered by intensity-modulated radiation therapy (IMRT), which is standard care in our hospital, to the planned target volume (PTV), which comprises the gross tumor volume (GTV) and clinical target volume (CTV). Target volumes are delineated on computed tomography (CT) scans, matched to- and combined with T2- and diffusion-weighted magnetic resonance imaging (DWI) according to published guidelines [20]. The CTV follows the mesorectal fascia up to the rectosigmoid curvature and stretches maximally to 4 cm caudal from the tumor, sparing the sphincter in case of a low anterior resection (LAR), or includes the sphincter complex +1-cm margin in case of an abdominoperineal resection (APR). The lymph node regions (internal iliac and obturator) stretch from the caudal end of the v. iliaca communis downward to the crossing of the internal iliac vessels under the m. piriformis, laterally limited by the pelvic muscles. The obturator region stretches from the m. obturatorius to the m. levator, ventrally limited by the ureter or dorsal side of the neurovascular bundle without inclusion of the vesiculae, uterus and vagina. Lateral and dorsal border are marked by the pelvic muscles and ventral iliac region. In addition, the presacral region stretches from the upper level of the iliac vessels to mesorectum, ventrally limited 2 cm from the sacrum, including the a. rectalis superior and excluding the neuroforamina. The PTV_CTV50_ is a non-uniform margin around the CTV according to local protocol consisting of an expansion of 13 mm ventrally, 9 mm dorsally, 10 mm laterally and 10 mm craniocaudally (Figure 2). The prescribed dose to the PTV_CTV50_ is that 95% of the prescribed dose should cover ≥99% of the PTV. Radiation is delivered with an external beam linear accelerator. For position verification, the sCRT protocol consists of cone-beam CT prior to the first three fractions and weekly thereafter.

**Figure 2 Fig2:**
[figure not shown]
**Cumulative dose plan of boost plus standard chemoradiation fractions (left) with associated dose volume histogram (right).** Delineations of gross tumor volume (GTV) plus planned target volume (PTV_GTV_) (red), clinical target volume (CTV) plus PTV (PTV_CTV_) (green), bladder (brown) and sigmoid (pink). Areas that receive a total dose of >65 Gy are represented in orange), and those that receive >50 Gy are shown in turquoise.

Capecitabine is administered orally twice daily on treatment days at a dose of 825 mg/m^2^, taken 2 hours before each radiation fraction and 12 hours later. Hematologic toxicity is tested every 2 weeks. Surgery is performed 10 to 12 weeks postradiation according to the Dutch guidelines [19]. The decision whether to perform total mesorectal excision surgery in form of LAR or APR, is made on the basis of the location and extensiveness of the tumor [21].

Two routine MRI scans are acquired using an MRI protocol developed in house, consisting of T2-weighted and DWI image sequences [22]. The first scan (taken maximally 2 weeks prior to radiation) is used for radiation planning, and the second (obtained 9 weeks postradiation) is used for preoperative response evaluation and surgical planning. Immediately prior to surgery, the surgeon will also perform a digital rectal examination (DRE) for clinical response evaluation.

### Boost intervention

The experimental boost intervention consists of 15 Gy (5 × 3 Gy on weekdays) to the GTV without concomitant chemotherapy. The boost is delivered in the week prior to the start of sCRT. A cumulative GTV dose of 65 Gy is delivered over the full treatment course of 30 fractions (6 weeks). This results in an equivalent dose in 2-Gy fractions of 66.3 Gy (α/β = 10 Gy) [23]. GTV delineation is based on T2-weighted and DWI scans; no CTV_GTV65_ margin is applied; and the PTV_GTV65_ is defined by a non-uniform margin of +11 mm in the anteroposterior direction, +7 mm in the lateral direction and +13 mm in the craniocaudal direction around the GTV, which represents tumor movement that was observed on in-house daily MRI scans and setup errors [24]. A volumetric modulated arc therapy stereotactic treatment plan is generated for boost patients, whereas IMRT is standard care used in the control arm, that accumulates the boost and standard chemoradiation doses (Figure 2). The maximally allowed cumulative dose within the GTV is 80 Gy (123% of 65 Gy), and the volume receiving 95% of the prescribed dose should be larger than 99% of the PTV_GTV65_. The maximum dose around, and dose prescription to, the PTV_CTV50_ is similar to the elective sCRT field (that is, 53.5 Gy). Daily online cone-beam CT scans are used for positioning before each boost fraction, and the sCRT position verification protocol follows thereafter.

Organs at risk (OARs) consist of the bowel bag (excluding sigmoid), bladder, vagina and anal sphincter. The dose constraints for the OARs remain unchanged for boost patients (namely, the dose to 1 cc of the OARs should be ≤53.5 Gy), and the volume receiving 45 Gy is aimed to be less than 195 cc for the bowel bag (excluding the sigmoid). OAR constraints are leading over PTV_GTV65_ coverage and may thus limit GTV dose if necessary. If dose prescriptions cannot be reached, a panel of radiation oncologists will discuss the feasibility and anticipated safety of the treatment plan and decide either to continue or to adapt the plan toward acceptable OAR constraints, taking into account anatomical limitations and planned surgery. One additional MRI scan is obtained in patients who receive the boost for response prediction purposes at the end of the second week (after ten fractions including the five boost fractions) and a rectoscopy for clinical response evaluation is performed in a subgroup of boost-arm patients that showed a ‘good’ response based on MRI.

### Primary endpoint

The primary endpoint of this study is pCR, which is classified according to the Mandard classification system as tumor regression grade 1 (TRG 1) [5] (that is, a sterile specimen with absence of residual cancer cells). Experienced gastrointestinal pathologists use a standardized protocol to evaluate the specimens [25], and central review of pathology is performed.

### Secondary endpoints

Secondary endpoints include non-complete pathologic responses (TRG 2–5), acute grade 3–4 toxicity, clinical response, surgical complications, QoL and disease-free and overall survival. The non-complete pathologic responses are categorized as good (TRG 1–2) or ‘not good’ (TRG 3–5) by the pathologist. A radiation oncologist will assess toxicity at weekly visits during the radiation treatment, as well as 4 weeks and 4 months after completion of sCRT. Toxicity is recorded according to the National Cancer Institute’s Common Terminology Criteria for Adverse Events, version 4.03 [26]. Long-term toxicity, (serious) adverse events (SAEs), hospitalization and other health-related problems are registered within the context of the PICNIC cohort during clinical follow-up and annual patient-administered questionnaires on health and oncological status. Clinical response evaluation is based on MRI (9 weeks after completion of chemoradiation; that is, the week before surgery) and DRE and rectoscopy, which are both performed right before surgery while the patient is under anesthesia. MRI and DRE are standardly performed in all patients, whereas rectoscopy is only performed in intervention arm patients who showed a good response based on MRI. For the MRI, a combination of T2-weighted and DWI sequences is used to measure residual tumor tissue in the initially delineated tumor region and its surrounding elective radiation field. Surgical complications are registered up to 30 days after the primary surgery in all patients and after closure of the diverting stoma in patients who previously underwent a LAR. For safety reasons, occurrence of anastomotic leakage is monitored closely in the LAR subgroup by daily review of postoperative patient charts for 30 days. QoL data are recorded by means of either online forms (Patient-Reported Outcomes Following Initial treatment and Long-term Evaluation of Survivorship (PROFILES): http://www.profilesregistry.nl/) or pencil-and-paper questionnaires. For this purpose, cancer-specific QoL questionnaires from the European Organization for Research and Treatment of Cancer (EORTC) are used, including the core (QLQ-C30 [27]) and colorectal cancer-specific (QLQ-CR29 [28,29]) questionnaires. The EORTC QLQ-C30 covers five functional scales, three symptom scales, a global QoL scale and six single items. The EORTC QLQ-CR29 assesses urinary, bowel and/or stoma, psychological and sexually related QoL issues, as well as side effects due to chemotherapy. These questionnaires are provided at the time of diagnosis (baseline) and 3, 6, 12, 18 and 24 months thereafter. Survival and disease-free survival are monitored within the PICNIC project through clinical follow-up records and via a link with the Dutch Cancer Registry. Disease-free survival is defined as the time in absence of a rectal cancer local recurrence or metastasis.

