### Data analysis

Data will be analyzed according to the intention-to-treat principle. Data of eligible patients who were randomly offered the boost (intervention arm) will be compared with eligible patients who were not randomly selected (control arm). In case of dropout (that is, no surgery following chemoradiation), a worst-case analysis will be performed in which all non-resected intervention-arm patients are classified as non-complete responders and all non-resected control patients are classified as complete responders. However, because omission of surgery is not common practice in our institution, we expect these numbers to be small. In case of substantial boost treatment refusal in the intervention arm, complier average causal effect analysis will be performed to deal with differences in compliance with treatment between both arms [31]. Outcomes include tumor pCR rate (TRG 1), good pathological response (TRG 1–2), clinical response, grade 3–4 toxicity, QoL, recurrence rates and disease-free and overall survival.

The primary outcome (proportion of patients with pCR) will be presented in proportions and compared by means of the χ^2^ test. Toxicity will be presented as the overall and/or time point-specific incidence of grade 3–4 toxicity, and differences will be tested with the χ^2^ test. QoL will be compared at multiple points in time. A relevant change in the patient’s perspective is indicated by a 10% difference or more than 0.5 of the standard deviation [32]. QoL data will be analyzed by mixed-effects models. Differences in disease-free and overall survival rates will be analyzed by Kaplan-Meier analysis and log-rank test. Differences with a *P*-value <0.05 are considered statistically significant, except for the primary endpoint, where *P* < 0.15 has been prespecified.

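### Clinical response is compared between arms, but rectoscopy, one of its three components, is done only in intervention-arm patients with a good MRI response

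*Protocol article*

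**What the plan says.** All references are to the protocol article.

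- *Secondary endpoints* sets out the components: "Clinical response evaluation is based on MRI (9 weeks after completion of chemoradiation; that is, the week before surgery) and DRE and rectoscopy". On who gets the first two, it says "MRI and DRE are standardly performed in all patients". The third component is restricted to part of one arm: "rectoscopy is only performed in intervention arm patients who showed a good response based on MRI".
- *Boost intervention* repeats the restriction and gives the purpose: "a rectoscopy for clinical response evaluation is performed in a subgroup of boost-arm patients", namely those whose MRI showed a good response.
- *Standard treatment* describes the routine work-up as a post-radiation MRI, after which "the surgeon will also perform a digital rectal examination (DRE) for clinical response evaluation". It names no rectoscopy.
- *Data analysis* compares patients offered the boost with eligible patients who were not selected. Its list of outcomes includes "clinical response, grade 3–4 toxicity, QoL, recurrence rates and disease-free and overall survival". Apart from the primary endpoint, the significance threshold is 0.05.

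**The concern.** Randomisation protects a comparison only if the outcome is ascertained in the same way in both arms. Here one component depends on the arm and, within that arm, on an earlier result. Take two patients with the same MRI and the same DRE, one in each arm. The intervention patient with a good MRI goes on to rectoscopy and the control patient does not. If the rectoscopy finding can alter the response category, the two can end up in different categories although nothing about their tumours differs.

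Intention-to-treat analysis does not repair this, because it governs who is counted in which arm and not how the outcome is measured. Nor can a later analysis supply the missing control-arm examinations, since they are never made. At stake is how the between-arm result on clinical response can be read: a difference, or the lack of one, could come partly from the extra test.

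**Working it through.** **1. The plan's own figure.** The article gives no rate, category or sample size for clinical response. Its only sample-size figure is 60 per arm for pCR, and that reproduces. The diluted intervention rate is 0.8 × 0.30 + 0.2 × 0.13 = 0.266. Comparing it with 0.13 at one-sided α 15% and 80% power (pooled variance, no continuity correction) gives 60 per arm, with power 80.1% at n = 60. Nothing here disturbs that calculation.

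**2. The sections side by side.**

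| Component | Intervention arm | Control arm |
|---|---|---|
| MRI, 9 weeks after chemoradiation | all | all |
| DRE before surgery | all | all |
| Rectoscopy before surgery | good MRI response only | none |

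All three rows are named as the basis of the endpoint, and the endpoint is among the compared outcomes. No section limits the comparison to the first two rows or calls rectoscopy exploratory.

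**3. Size of the artefact under no treatment effect.** Every value of g and o below is an assumption.

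- g = proportion with a good MRI, the same in both arms: 0.30 to 0.40.
- o = proportion of those whose classification rectoscopy overturns, over and above any overturned by DRE: 0.10 to 0.30.
- s = share of the intervention arm open to rectoscopy: 1 if everyone offered the boost counts, 0.8 if only those who accept it do. The 20% refusal is the article's own expectation.

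Let R be the response rate by MRI and DRE. The control rate is R and the intervention rate is R − g·o·s, so the spurious gap is g·o·s.

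| g | o | gap, s = 1 | gap, s = 0.8 |
|---|---|---|---|
| 0.30 | 0.10 | 0.030 | 0.024 |
| 0.40 | 0.20 | 0.080 | 0.064 |
| 0.40 | 0.30 | 0.120 | 0.096 |

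The range is 3–12 points, or about 2.4–9.6 points if refusers are not examined. *Secondary endpoints* speaks of the intervention arm and *Boost intervention* of the boost arm, so the text does not settle which value of s applies.

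**4. Scale.** Take the middle row with s = 1, and suppose DRE overturns nobody. The rates are 40% and 32%. With 60 per arm the standard error of the difference is √(0.40 × 0.60/60 + 0.32 × 0.68/60) = √0.00763 = 0.087. The 8-point artefact is then about 0.9 of a standard error (0.08/0.087), or 4.8 of 60 patients.

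**5. Sensitivity to the assumptions.** A second model assumes equal true response c in both arms, MRI plus DRE with 80% sensitivity and false-good rate f, and rectoscopy that can only confirm or downgrade.

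- Smallest gap: c = 0.30, f = 0.10, rectoscopy sensitivity 1.0 and specificity 0.5. Control 0.24 + 0.07 = 0.310; intervention 0.24 + 0.035 = 0.275; gap 3.5 points; rejection rate about 7% at two-sided 0.05.
- Largest gap: c = 0.13, f = 0.30, sensitivity 0.9 and specificity 0.8. Control 0.104 + 0.261 = 0.365; intervention 0.0936 + 0.0522 = 0.146; gap 21.9 points; rejection rate about 79%.

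The largest case implies that rectoscopy overturns 60% of good classifications (0.219/0.365), well beyond the range in step 3. The spread shows that the size is set by inputs the article does not provide.

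**6. Direction.** Steps 3 to 5 let rectoscopy only downgrade. If it were used to upgrade doubtful responses to complete ones, the gap would favour the intervention arm.

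**The case against.** The strongest reply is that bias needs a rule the article never states. It gives no response categories, no hierarchy among the three tests and no way of combining them. It names tests for pCR, toxicity, quality of life and survival, but none for clinical response. How the components become an analysed variable is the kind of detail an article leaves to the full protocol or analysis plan, and a comparison on MRI and DRE alone would be free of the problem. This stands as far as it goes: a reader might infer that the comparison is biased by a known amount, and the text does not show that. It does not dispose of the point, because the article positively fixes an asymmetric assessment and says the endpoint rests on it.

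The magnitude is also open to challenge. If the overturn rate were not net of DRE, the product would overstate the gap, and if refusers are not examined it shrinks by a fifth. Both corrections are right and are built into the working.

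A reader might further infer that a spurious difference here would steer the next trial. The documents do not support that. *Background* and *Discussion* link good clinical response to future organ preservation, but no section makes the between-arm difference a trigger for anything. *Sample size considerations* sizes the study on pCR, and *Discussion* takes pathology as the reference standard, with which clinical response can then be correlated. That within-patient correlation does not need identical measurement across arms, though it should keep rectoscopy separate from MRI and DRE.

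Finally, the statement "Data will be analyzed according to the intention-to-treat principle" does not by itself show the error. The relevant text in that section is the list of outcomes and the definition of the two groups compared.

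**Conclusion.** The point holds in conditional form. Read as written, the article lets a compared secondary endpoint draw on a test given in one arm only, and only after a good MRI. To the extent that rectoscopy enters the compared classification, allocation alone can change a patient's category.

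The 3–12 points (about 2.4–9.6 without refusers) are an illustration. They rest on assumed good-MRI and overturn rates, on the overturn rate being net of DRE, on no treatment effect, and on rectoscopy only downgrading. Neither the size nor the sign can be read from the article.

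The scope is one secondary endpoint in a trial that calls itself exploratory. A reader might extend the doubt to the main result, but pCR and good pathological response (TRG 1–2) are judged on the surgical specimen and do not depend on rectoscopy. The point is worth acting on because the remedy is cheap and the missing control-arm data cannot be recovered afterwards.

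**What to change.** Add one sentence to the endpoint definition: for the between-arm comparison, clinical response is classified from MRI and DRE only, by the same rule in both arms, with the DRE result recorded before any rectoscopy. The order of recording matters because DRE and rectoscopy take place in the same session under anaesthesia, so the DRE reading could otherwise be influenced by what rectoscopy shows.

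Report rectoscopy descriptively within the intervention arm, for example as its correlation with pathology, and keep it out of the arm comparison. State whether patients who decline the boost count among those eligible for it, so that *Secondary endpoints* and *Boost intervention* agree.

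This adds no procedure or visit. The cost is that the compared endpoint does not use the rectoscopy information.
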